## Abstract

**Background:**

Basal cell carcinoma is the commonest human cancer. Despite increasing incidence it remains poorly researched. While not life threatening it can cause significant cosmetic disfigurement. Imiquimod, a cream which enhances the body's immune response, may help deal with the number of cases that occur in low-risk sites, especially when good cosmetic results and home use without surgery are needed.

This study aims 1. To compare excisional surgery with imiquimod cream for nodular or superficial basal cell carcinoma in low risk sites, with respect to 3 year clinical clearance, cost-effectiveness and cosmetic results. 2. To ascertain if certain phenotypic features and gene polymorphisms predict tumour responsiveness to treatment.

**Methods/Design:**

Five hundred participants with low risk nodular or superficial basal cell carcinoma will be recruited from hospitals to this multi-centre, randomised, parallel group, controlled phase III trial. Treatment in the imiquimod group is for 6 weeks for superficial basal cell carcinoma and 12 weeks for nodular basal cell carcinoma. Both treatment groups are followed up in clinic for 3 years. Primary outcome variable: the proportion of participants with clinical evidence of success (no recurrence) at 3 years. The primary outcome will be compared between the two treatment groups. Secondary outcomes include: i) clinical success at 1, 2 and 5 years, ii) time to first recurrence, iii) cosmetic appearance of lesion site after treatment, iv) level of pain, and v) cost-effectiveness. Safety and tolerability data will also be reported.

**Discussion:**

This study protocol describes a pragmatic randomised controlled trial which it is hoped will address the above uncertainties. Three-year results will be available towards the end of 2010.

**Trial registration:**

Meta-register: NCT00066872, Eudract No. 2004-004506-24, ISRCTN48755084.

## Background

Basal cell carcinoma (BCC), or "rodent ulcer" is the commonest human cancer [1-3] affecting at least 30,000 UK people annually, with increasing incidence [4], especially in younger people [5] and in those with higher social class [6]. Although not life threatening, BCC can cause significant cosmetic disfigurement, and remains one of the most poorly researched human cancers [7]. Most BCCs are treated surgically in hospitals, but current treatment provision is becoming saturated in many centres in the UK. A systematic review highlighted topical imiquimod as a potentially useful therapy for superficial basal cell carcinoma and raised the possibility that it could also be useful for dealing with the bulk of low risk nodular basal cell carcinomas - thereby releasing limited surgical resources in the UK dermatology centres to tackle more complicated tumours at high risk sites.

Imiquimod cream enhances the body's immune response. Although not as effective as surgery, it may result in a better cosmetic result (potentially important as a majority of BCCs appear on the face and neck [8,9]) together with the added convenience of home application.

Prior to this study, imiquimod cream was not used routinely for BCC, and clinical opinion was divided regarding its potential usefulness for different types of BCC. It is thus timely to consider these issues to prevent assimilation of practice without adequate evaluation.

If imiquimod 5% cream has an acceptable success rate, is cost-effective and easy to use, then it could be an effective treatment option for the routine first treatment of the majority of low risk nodular and superficial BCCs seen in skin cancer clinics in the UK and elsewhere. Recurrences and high risk BCCs could then be dealt with surgically by dermatologists and plastic surgeons working as part of the skin cancer teams. Treatment with imiquimod could even start in the community after histological diagnosis, using a strict protocol to prevent indiscriminate use (and diagnostic uncertainty and/or possible delay in melanoma diagnosis) and hence increase in costs.

## Methods/Design

### Trial objectives

We seek to answer the following questions:

1. Can imiquimod 5% cream applied topically give an acceptable and clinically useful success rate (3 year clinical clearance) and acceptable side effect profile when compared with excision surgery for superficial and nodular BCC at low risk sites?

2. Is imiquimod more cost effective than surgery for low-risk BCC?

3. Does imiquimod result in a more aesthetically acceptable result than conventional excision?

4. Do certain phenotypic features and gene polymorphisms predict tumour responsiveness to treatment?

We hypothesise that the clinical success rate at 3 years among participants treated with imiquimod cream will not be inferior to the clinical success rates obtained from surgery.

Both nodular and superficial BCC are included in this trial because in real life clinicians are unlikely to make an *a priori *decision on what constitutes a nodular and superficial lesion, and even if they do, their clinical decision may be wrong (compared to histology, which is also somewhat arbitrary). The agreement between clinical and histopathological diagnosis will be looked at.

Long-term follow-up is needed to catch late recurrences of slower-growing tumours [10-13]. There is a real danger that lesions that appear clear in the short term e.g. at 1 year, will recur in the long term. It is also unclear whether the short-term histological clearance reported in the Phase II studies can be translated into a durable clinical clearance, and there may be a gradient of treatment response depending on the histological subtype. More precise estimates of treatment efficacy using much larger sample sizes are needed for the commoner nodular BCC. A definitive independent trial with cost-effectiveness data and long term follow up will help to inform patients, health care workers and the NHS. Information on possible predictors (clinical and genetic) of treatment response might also be useful for guiding clinical practice.

### Trial design

Prospective, multi-centre, randomised, parallel group, controlled phase III trial, to compare excision surgery and imiquimod cream for nodular and superficial basal cell carcinoma presenting in low risk areas [3]. This is a simple pragmatic study [14].

The consultant dermatologist will decide if the lesion is superficial or nodular at the study outset (confirmed by the diagnostic biopsy result).

### Trial interventions

1. Imiquimod 5% cream once daily for 6 (superficial - clinically diagnosed) or 12 (nodular) weeks total, or

2. Surgical excision with a 4 mm margin (accepted standard at trial set-up). The surgical group will be operated on as soon as local conditions permit.

Treatment failures (after either a biopsy or a period of watchful waiting) will be treated by surgical excision. Treatment duration and frequency of dosing are based on results of existing studies [15] at study set-up, and a balance of efficacy with effort for the participants and possible side effects. The dosing frequency was unchanged after the manufacturers presented results from a large dose-finding clinical study to us, however after the start of this study imiquimod became licensed for superficial BCC, with a 5 days per week dosing frequency.

In order to identify possible genetic markers for tumour response, 5 ml of blood will be taken from consenting participants. Methods for analysing the genetic marker data are given in a separate genetic markers addendum to the protocol.

### Treatment adherence

In the imiquimod group local reactions and the long duration of daily treatment are factors which could compromise compliance. The application of the cream will be explained. Cards for monitoring daily pain will be given to participants in both groups, and returned every six weeks. A telephone help-line will be available for answering day to day problems. Participants will be asked to return used and unused imiquimod sachets (one per day of treatment).

### Participant selection

At each of 12 (initially three) hospitals potentially suitable participants will be asked to speak to the research nurse, who explains the study, checks eligibility and deals with informed consent. Entry criteria are as broad and inclusive as possible in order to approximate the sort of patients encountered outside the usual strict clinical trial environment and hence to improve external validity.

#### Inclusion criteria

• Men and women of any age who present clinically with either primary nodular or superficial BCCs, or a skin lesion other than BCC which turns out on histology to be a superficial or nodular BCC

• Any number of BCCs (although only one per participant is selected for the study)

• Histologically proven BCC (usually a punch or shave biopsy specimen of no more than 25% of the total lesion, though sometimes at surgery)

• Location of primary nodular/superficial BCC in low risk areas (avoiding use of imiquimod in areas at high risk of recurrence where delay of appropriate surgery might result in more invasive procedures)

• Informed consent

• Must have access to a telephone

#### Exclusion criteria

• Genetic or nevoid conditions such as Gorlin's syndrome

• Morphoeic (microinfiltrative) trial lesion as diagnosed clinically (even if not histologically classed as morphoeic - histological sample may have missed infiltrative nature of lesion)

• Allergy to any of the interventions

• Involvement in a trial of another experimental intervention

• Life threatening disease

• Bleeding disorders

• Not available for follow up for 3 yrs

• Pregnant, intention to become pregnant during treatment phase of the trial, or breastfeeding

### Outcome measures

#### Primary

The proportion of participants with clinical evidence of "success" (defined as absence of treatment failure or any signs of local recurrence) at 3 years as judged by a consultant dermatologist, as would occur in routine clinical practice. Participants allocated cream, that subsequently require surgery for poor response or recurrence will be counted as treatment failures, if histology is proven to be positive.

#### Secondary

i) The proportion of participants with clinical success at one, two and five years.

ii) Time to first recurrence (classified into one of the following 5 categories according to the period between follow up visits when this occurred: "prior to year 1 visit"; "between year 1 visit and year 2 visit"; "between year 2 visit and year 3 visit"; "between year 3 visit and year 5 visit"; "no recurrence prior to year 5 visit"). The actual time of recurrence is not known, but only the visit at which it is diagnosed.

iii) The proportion of participants with a lesion of excellent or good appearance at 6 months and at 3 years. (The cosmetic appearance of a participant's lesion will be rated independently by the participant and blinded observer. using a five point scale ("Excellent", "Good", Fair", Poor", "Very poor")).

iv) The proportion of participants experiencing a moderate or more severe level of pain a) during treatment and b) in the 16 weeks following treatment. (This will be measured daily using a six-point scale ("No pain", "Mild", "Mild-Moderate", "Moderate", "Moderate-Severe", "Severe") using a questionnaire completed at home).

v) Cost effectiveness to include number of participant visits to hospital, as well as cost of treatment per session.

Clinical clearance will not be routinely confirmed by further biopsy mainly because a) this would not happen in clinical practice and b) participants benefitting from an excellent cosmetic result in the cream group are unlikely to want a biopsy scar. If, however, the clinician is concerned there is a recurrence, then he/she will biopsy that lesion exactly as would happen in routine follow-up care from other treatment modalities.

**Adverse events **will be collected from all participants up to the 1 year visit, thereafter only events considered serious or related to the trial comparators (imiquimod or surgery) will be collected.

### Health service research issues

An economic evaluation will include:

1. A cost-comparison analysis (net impact of all resource changes) of the two treatment strategies.

2. A cost-effectiveness analysis presented in the form cost per 'cleared participant'.

3. A valuation (in monetary terms using willingness to pay) of the perceived benefits of both treatment strategies, which (depending on results) could be incorporated into a cost-benefit analysis.

### Follow-up of outcome measures

The nurse will make a telephone call to the participant at two weeks to discuss any early problems, followed by clinic follow-up at 6, 12, and 18 weeks, 6 months, 1, 2 and 3 years. The dermatologist will also see the participant briefly, at 12 weeks (surgery only), 18 weeks (superficial, imiquimod only), 6 months (nodular, imiquimod only), 1, 2 and 3 years. A postal follow-up of documented recurrences at 5 years will be conducted by writing to GPs, hospital clinics and obtaining pathology records. See figure 1.

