#### Secondary outcome measures

**Clinical success **at 1, 2 and 5 years will be analysed and presented in the same way as for the primary outcome variable.

**Time to first recurrence (five categories):** Comparison of treatment groups will use ordinal regression analysis, adjusting for centre and BCC type (fixed effects). The number and percentage of participants in each of the 5 time of first recurrence categories will be reported by treatment group. The odds ratio arising from the continuation ratio model and the corresponding 98% confidence interval will be reported.

**Cosmetic appearance** of lesion site at 6 months and at 3 years as rated by the participant and by an independent dermatologist. The analysis of primary interest will be the participants rating at 6 months, focusing on head and neck, and then on all sites. The analysis of the dermatologist's ratings will be based on lesions at all sites. For each of the cosmetic appearance outcome measures, the number and percentage of participants with a lesion of excellent or good appearance in each treatment group, the absolute difference in percentages between groups and the corresponding 98% confidence interval for the absolute difference in percentages will be reported. The relative risk of having a lesion of excellent or good appearance in the imiquimod group relative to the surgery group and the corresponding two-sided 98% confidence interval will be presented. The inclusion of baseline variables in the model will be explored.

**Level of pain:** for each of the treatment period and the 16 week follow-up period, the number and percentage of participants who experience the following levels of pain (moderate or more severe, mild-moderate or less severe pain, no pain) will be reported by treatment group. The median number of days of moderate or more severe pain will also be reported.

**Cost effectiveness** for the different treatment modalities will be explored.

**Treatment compliance** in the imiquimod group will be reported. The amount of imiquimod cream used will be estimated from the daily diary (number of days of exposure). Insufficient exposure to imiquimod cream will also be reported (<4 weeks treatment for superficial BCCs; <8 weeks treatment for nodular BCCs), also the number unable to complete the full course as a result of an adverse event. In the surgery group treatment compliance will be the receipt of excisional surgery.

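### The 5-year outcome is labelled and analysed as clinical success, but no examination follows year 3 and a records search can show only that no recurrence was documented

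*Protocol article*

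**What the plan says.** All references are to the Protocol article.

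- **Outcome measures, Primary.** Success means no treatment failure and no sign of local recurrence at 3 years, "as judged by a consultant dermatologist, as would occur in routine clinical practice".
- **Outcome measures, Secondary, item i.** "The proportion of participants with clinical success at one, two and five years". No separate definition of success is given for 5 years.
- **Outcome measures, Secondary, item ii.** Time to first recurrence has five categories. Two are bounded by a year 5 visit, the last being "no recurrence prior to year 5 visit". The item adds: "The actual time of recurrence is not known, but only the visit at which it is diagnosed".
- **Abstract (Methods/Design) and Follow-up of outcome measures.** Clinic follow-up lasts 3 years, and the last listed nurse and dermatologist contacts are at 3 years. For 5 years the text gives one source: "A postal follow-up of documented recurrences at 5 years will be conducted by writing to GPs, hospital clinics and obtaining pathology records".
- **Statistical analysis, Secondary outcome measures.** The sentence on the success rates reads: "at 1, 2 and 5 years will be analysed and presented in the same way as for the primary outcome variable".
- **Statistical analysis, Missing data.** Worst-case and best-case analyses are stated for the primary outcome.

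**The concern.** Success at 1, 2 and 3 years rests on someone looking at the treated site. At 5 years nobody is scheduled to look. A search for documented recurrences can establish a failure, but it cannot establish that a site is clear. The two measurements share one label and one analysis, and the time-to-recurrence outcome is written as if a fifth-year examination took place.

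What is at stake is the claim about durability. The Trial objectives section justifies long follow-up by the need to catch late recurrences of slow-growing tumours, and it warns that sites clear at 1 year may recur later. The 5-year outcome serves that purpose with the weakest ascertainment of any time point. Set beside the 1-, 2- and 3-year rates under the same name, it would be read as an examined result.

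**Working it through.** **Step 1: compare the passages.**

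| Feature | Years 1, 2 and 3 | Year 5 |
|---|---|---|
| Contact | Clinic visit, seen by dermatologist | None scheduled |
| Source | Judgement at the visit | GP, hospital clinic and pathology records |
| What the data can show | Failure, or no sign of recurrence | Failure, or no recurrence on record |
| Label | Clinical success | Clinical success |
| Analysis | Robust Poisson model, relative risk, 98% interval | The same |

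The year 5 visit in Outcome measures conflicts directly with the schedule in Follow-up of outcome measures. The Secondary section also says that biopsy follows only when a clinician is concerned about recurrence. A pathology record therefore depends on a prior examination, and after year 3 the trial arranges none.

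**Step 2: who is classed as a success.** A participant whose records are returned without a recurrence can only be classed as free of recorded recurrence. If a recurrence occurred but was not noticed, not presented or not filed, that participant counts as a success. This follows from the text. The coding of a participant with no return at all is not stated.

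**Step 3: possible effect on the relative risk.** The article gives no 5-year figure to reproduce. The starting values are its 3-year design rates (Sample size): surgery 97%, imiquimod 90%, so RR = 0.90/0.97 = 0.928. Late failures in years 3 to 5 (x, in percentage points of all participants) and the share captured by records (c) are assumptions.

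Observed 5-year success in each arm = 3-year success − c × x.

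| x, surgery / imiquimod | c, both arms | Surgery | Imiquimod | RR | Shift from full capture |
|---|---|---|---|---|---|
| 1 / 3 | 100% | 96.0% | 87.0% | 0.906 | – |
| 1 / 3 | 80% | 96.2% | 87.6% | 0.911 | +0.004 |
| 1 / 3 | 50% | 96.5% | 88.5% | 0.917 | +0.011 |
| 1 / 3 | 0% | 97.0% | 90.0% | 0.928 | +0.022 |
| 2 / 5 | 100% | 95.0% | 85.0% | 0.895 | – |
| 2 / 5 | 80% | 95.4% | 86.0% | 0.901 | +0.007 |
| 2 / 5 | 50% | 96.0% | 87.5% | 0.911 | +0.017 |
| 2 / 5 | 0% | 97.0% | 90.0% | 0.928 | +0.033 |

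**Step 4: direction.** With equal capture, RR(c) = (0.90 − c·x_I)/(0.97 − c·x_S). It rises as c falls only if x_I/0.90 > x_S/0.97, that is, only if late failure among 3-year successes is more frequent on imiquimod. With unequal capture the direction is open. For x = 2 / 5:

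- 50% captured after surgery, 90% after imiquimod: (0.90 − 0.045)/(0.97 − 0.010) = 0.855/0.960 = 0.891, a shift of −0.004.
- 90% captured after surgery, 50% after imiquimod: (0.90 − 0.025)/(0.97 − 0.018) = 0.875/0.952 = 0.919, a shift of +0.024.

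**The case against.** The strongest reply has four parts.

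1. **The source is disclosed.** The follow-up section says openly that 5-year data are documented recurrences, a legitimate choice in a pragmatic trial. This stands. The fault lies in the label and in the visit that does not exist, not in using records.
2. **Same analysis need not mean same ascertainment.** The sentence on 1, 2 and 5 years sits in the statistics section and most naturally refers to the model and the reporting format. Using one model for data from two sources is no error in itself. This also stands, but the Secondary outcome list separately calls the 5-year result clinical success without redefining it.
3. **Records suit the failure definition.** Imiquimod participants who go to surgery count as failures only with positive histology, which pathology records would hold, and GPs and consultants are told of participation. This makes a documented failure credible. It does not make an empty record evidence of a clear site.
4. **Coding may be in the analysis plan.** The article is a summary and refers to a separate plan. A reader might infer that participants with no return, or those who missed the year 3 visit, become 5-year successes on silent records. The article does not say so, and that inference should not be drawn. The separate plan cannot, however, reconcile the article's year 5 visit with its postal search.

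**Conclusion.** The point holds as a mismatch between what the 5-year outcome is called and what is measured. It concerns secondary outcomes only. The Non inferiority margin paragraph confines the 0.87 margin to the primary outcome, so neither that margin nor the 3-year result is affected.

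A reader might go further and infer that the 5-year comparison is biased in favour of imiquimod. The documents do not support that. They give no late recurrence rate by arm and no capture rate. A shift toward 1 needs similar capture in both arms and more late failure on imiquimod. Under the assumed rates and equal capture of 80% to 50%, the shift is about 0.004 to 0.017, and at most 0.033 if nothing is recorded. Size and direction in the trial itself are unknown. The textual conflict is certain and does not depend on these figures.

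**What to change.** - Rename the 5-year outcome *no documented failure or recurrence by 5 years*, and report it separately from the examined 1-, 2- and 3-year rates.
- In the time-to-recurrence categories, replace the year 5 visit with the 5-year records search, and qualify the statement that recurrence is timed by the visit of diagnosis.
- State the classification. Earlier failures remain failures. Everyone else is classified from a GP, hospital or pathology return that covers the period to 5 years. Participants with no such return are missing, not successes, and best-case and worst-case analyses are extended to this outcome.
- Add a sensitivity analysis restricted to participants examined and free of failure at the year 3 visit. Year-3 non-attenders are then handled alike whether or not a recurrence is later documented. This subset is formed after randomisation, so the analysis is supportive only.

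The cost is wording in the protocol and analysis plan plus one extra analysis, with no new visits or data. The price is a smaller 5-year denominator and a weaker label. The change makes the claim accurate, but under-recording in returned records remains and should be stated as a limitation.
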